## Methods/Design

### Study design

This is a community-based controlled and longitudinal study. The study population will be comprised of HIV-infected females commencing ARV treatment at two Lusaka Urban clinics, Matero Reference Clinic (MRC) and Matero Main Clinic (MMC). The study participants will be allocated to either the experimental group and receive HEPS or control group and not receive HEPS. Participants will be randomly assigned to either group by the sister-in-charge at each clinic. Data will be collected at four time points across the 12-month study: baseline (0 months), 4-months, 8-months and 12-months follow-up. The study protocol has been approved by the University of Zambia Research Ethics Committee (approval ref 017-02-07).

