### Allocation to study groups

On the day of recruitment (baseline) after completing all body composition assessments and physical examination, the sister-in- charge will cut pieces of papers, equal to the number of participants enrolled that day. Half of the papers will bear the word 'Soya' while the other half will have 'No Soya' written on them. The papers will be folded several times to conceal the writing and then mixed. Each participant will be asked to pick one and read loud for the sister-in-charge to record the group assignment in the study registry book.

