### Sample size calculation

The sample size calculations were based on detecting a 5% weight change between groups over the 12-month period. Assuming a 10% variance in the within-group body weight, 37 participants are needed in each group to detect this difference with an alpha of 0.05 and a power of 90%. If the attrition is 25% over the year, a minimum of 48 participants are required in each group. Assuming FFM is 35% of the weight gain [22], 44 participants are needed in each group to detect this difference with an alpha of 0.05 and a power of 90%. If the attrition is 25% over the year, a minimum of 58 participants are required in each group. It is uncertain what magnitude of change is expected in CD4 counts and viral load. For a moderate effect size (Cohen's d = 0.4) 66 participants are needed in each group to detect this difference with an alpha of 0.05 and a power of 90%. If the attrition is 25% over the year, a minimum of 88 participants are required in each group.

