### Statistical Analysis plan

Statistical analyses will be performed using SAS software (SAS Institute, Cary, NC, USA). Descriptive statistics will be provided for the nutritional status, body composition, clinical and socio-demographic characteristics of the participants at baseline, 4, 8 and 12 months follow-up. At baseline, the characteristics of participants on food supplement and those without food supplement will be compared using t-test for continuous variables and Fisher's Exact Test for categorical variables. Repeated measures analysis of variance (RM-ANOVA) will be employed to compare the primary outcome variables (nutritional status and body composition) in participants with and without food supplements. Where confounding variables may need to be account for, adjustment will be made by covariance.

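### Covariate adjustment is left conditional and unnamed alongside baseline significance tests; the outcome's baseline value and clinic should be fixed in every outcome model, with baseline used once

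*Protocol article*

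**What the plan says.** Three statements in the article's Statistical Analysis plan section matter here.

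- Baseline: characteristics of the two arms "will be compared using t-test for continuous variables and Fisher's Exact Test for categorical variables".
- Primary comparison: "Repeated measures analysis of variance (RM-ANOVA) will be employed to compare the primary outcome variables (nutritional status and body composition", with and without the supplement.
- Adjustment: "Where confounding variables may need to be account for, adjustment will be made by covariance".

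The section names no covariate and gives no rule for deciding when one is needed. It does not say whether the baseline value is one of the repeated responses or a covariate, or which RM-ANOVA contrast carries the treatment test. Clinic does not appear in it.

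The design facts are in other sections. Under Study design, "Participants will be randomly assigned to either group by the sister-in-charge at each clinic", and "Data will be collected at four time points across the 12-month study: baseline (0 months), 4-months, 8-months and 12-months follow-up". Under Allocation to study groups, papers are prepared for each day's enrolment: "Half of the papers will bear the word 'Soya' while the other half will have 'No Soya' written on them".

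**The concern.** Allocation is by random draw. If the draw is carried out as described, a significant baseline difference reflects chance, so the tests do not show which variables need adjustment. Confounding in the observational sense is also not the reason to adjust in such a trial. The reasons are precision and fidelity to the design, and both can be settled in advance.

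As worded, the rule lets the primary model be chosen once data are in hand, and more than one result could then be presented as primary. It also fails to secure the two adjustments that the design supports: the baseline value of each outcome, and clinic, within which allocation is done. Depending on the contrast tested, the first of these can be worth a great deal of power or very little.

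**Working it through.** **Inputs from the article.** Total sample 200 (Dietary intake study section) and half-and-half allocation, so about 100 per arm. Attrition of 25% (Sample size calculation) leaves 75 per arm. Effect sizes from Sample size calculation: d = 0.4, stated for CD4 count and viral load; and for weight, "detecting a 5% weight change between groups over the 12-month period" with "Assuming a 10% variance in the within-group body weight", which gives d = 0.5 if the 10% is read as a standard deviation.

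**Assumptions, not in the article.** Rho of 0.5, 0.7 or 0.8, equal between all pairs of visits; two-sided alpha of 0.05; a treatment effect that is zero at baseline and constant at the three later visits.

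**The article's own figures.** It gives no power figure for the RM-ANOVA, so there is none to reproduce. Its stated 66 per group for d = 0.4 at 90% power is not the two-group result: 2 × (1.96 + 1.2816)² / 0.4² = 131.3, or 132 per group. That is a separate matter; only the effect sizes are used here.

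**Formulas.** For the first three analyses, power = Φ(δ − 1.96) + Φ(−δ − 1.96), with δ = (effect / f) × √(75/2) and √(75/2) = 6.124. With d = 0.4:

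- ANCOVA of the mean of the three follow-up visits: effect 0.4, f = √((1 + 2ρ)/3 − ρ²) = 0.6455, 0.5568, 0.4761; δ = 3.79, 4.40, 5.14.
- ANCOVA at 12 months only: effect 0.4, f = √(1 − ρ²) = 0.866, 0.714, 0.600; δ = 2.83, 3.43, 4.08.
- RM-ANOVA group main effect over four visits: the effect is diluted to ¾ × 0.4 = 0.3, f = √((1 + 3ρ)/4) = 0.7906, 0.8803, 0.9220; δ = 2.32, 2.09, 1.99.
- RM-ANOVA group-by-time: noncentral F on 3 and 3 × 148 = 444 degrees of freedom, λ = (75/2) × 0.75 × 0.4² / (1 − ρ) = 4.5 / (1 − ρ) = 9.0, 15.0, 22.5.

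| Analysis, 75 per arm | d = 0.4, rho 0.5 / 0.7 / 0.8 | d = 0.5, rho 0.5 / 0.7 / 0.8 |
|---|---|---|
| ANCOVA, follow-up mean | 97% / 99% / >99% | >99% / >99% / >99% |
| ANCOVA, 12 months only | 81% / 93% / 98% | 94% / 99% / >99% |
| RM-ANOVA, group-by-time | 71% / 91% / 99% | 89% / 99% / >99% |
| RM-ANOVA, group main effect | 64% / 55% / 51% | 83% / 74% / 70% |

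**Shape of the effect.** A constant effect favours averaging. If the effect grew linearly to d = 0.4 at 12 months, the follow-up mean would carry ⅔ × 0.4 = 0.267, so δ = 0.267 × 6.124 / f = 2.53, 2.93, 3.43 and power is about 72%/83%/93%. Group-by-time then has 56%/80%/94% and the main effect 34%/28%/26%. The ordering is the same, except that at rho 0.8 the follow-up mean and group-by-time are level.

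**Discretion over covariates.** A null simulation (8,000 runs, 75 per arm, assumed rho 0.7 and four weak covariates) gave these rejection rates at nominal 5%: fixed unadjusted 5.0%; fixed ANCOVA 4.7%; adjusting for baseline only when its baseline test is significant 3.6%; taking the smallest p-value from seven covariate sets 13.0%. Simulation error is about √(0.05 × 0.95 / 8000) = 0.24 percentage points.

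**Baseline tests.** With 10 to 20 independent characteristics, the chance of at least one p < 0.05 is 1 − 0.95¹⁰ = 40% to 1 − 0.95²⁰ = 64%. Weight, BMI, fat mass and skinfolds are related, so independence is unrealistic and these figures are only a guide.

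**The case against.** The strongest reply is that RM-ANOVA on four visits may already use the baseline value. If baseline is a response level and group-by-time is tested, the contrast is built on change from baseline. The table bears this out: at rho 0.7 to 0.8 little is left to gain. A reader might infer a large gain at any rho by setting ANCOVA against a comparison of follow-up values alone (69% at d = 0.4), but the article plans no such test. This part of the reply stands.

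A reader might also infer that the baseline tests select the covariates. The section sets the two side by side without linking them, so the 40% to 64% figure says nothing direct about the primary result. Nor is the 13.0% a forecast: the article does not propose picking the smallest p-value, and the one test-then-adjust rule simulated was conservative.

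Clinic should not confound either. The draw is balanced, or nearly so, within each clinic's enrolment day, and leaving clinic out tends at most to make the test conservative. Likewise, nothing in the article proposes adjusting for dietary intake, which is recorded after the 8-month visit; the wording merely does not rule it out.

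Finally, an article may leave the list of covariates to a fuller plan. That covers silence, but this section states a conditional rule and states the baseline tests, and both are poor choices as written.

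**Conclusion.** The point holds in a limited form. The stated rule leaves the primary model open after data are seen, the baseline p-values serve no useful purpose in a randomised comparison, and the plan commits to neither the outcome's baseline value nor clinic.

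No single figure for lost power can be given, because the article fixes neither the contrast nor rho. Under the assumptions above at d = 0.4, adjusting the follow-up mean for baseline gains 33 to about 49 percentage points over the four-visit main effect, about 26 points over group-by-time at rho 0.5, and 8 points or fewer over group-by-time at rho 0.7 or above. The benefit of including clinic cannot be computed from the document; the reason to include it is that the model should reflect how allocation was done.

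**What to change.** - Analyse the 4-, 8- and 12-month values as responses in a repeated-measures model. Include the baseline value of that outcome and clinic (MRC or MMC) as fixed covariates in every outcome model, and state which contrast carries the treatment test. Alternatively, keep baseline among the responses with its mean constrained equal across arms. Either way baseline is used once; adding it as a covariate to an RM-ANOVA that already has it as a response would use it twice.
- Present baseline characteristics by arm without p-values.
- Label any further adjustment as sensitivity analysis, and limit it to variables measured before allocation.

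The cost is a small restructuring of the model as well as new wording. No new data, participants or procedures are needed, since baseline outcomes and clinic are already recorded.

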## Discussion

Few studies have used comprehensive anthropometric and criterion body composition assessment techniques to assess the impact of food supplements in Zambian HIV-infected women receiving ARV treatment and indeed elsewhere in sub-Saharan Africa. The outcome of this study will thus provide Zambia and the region with valuable information that will help guide the development of appropriate nutrition guidelines for PLHA, especially in the context of the risk for obesity and the metabolic syndrome in this population.

BIA is a rapid, inexpensive and non-invasive method to measure body composition and of particular interest for field and clinical studies in this setting. The ability to utilise criterion measures of nutritional status in these people will provide important information to inform more appropriate nutritional interventions and the provision of improved clinical care and support using validated approaches.

Despite the potential benefits of the BIA technique, a limitation is the inability to identify site-specific alterations in body fat, a particular issue in PLHA [23]. Skinfold thickness measurements provide information on regional and whole body composition and hence may be approach to consider visceral fat accumulation and fat loss from limbs, of clinical concern due to the relationship with insulin resistance and other serious metabolic disturbances [24].

One of the limitations of the proposed study is that only female participants will be included. Due to gender differences in body composition and HIV-associated wasting, results will not be readily applicable to HIV-infected males [25] and children.
